##### Other surveillance data

The changes in rates of positive screening and clinical isolates will be examined as per the primary outcome.

##### Changes in patient perceptions of hospital cleanliness

As there are likely to be differences in the questions used between hospitals, we will estimate the change within each hospital and then combine these using a meta-analysis. To provide estimates on a common scale, we will look at the percentage change from baseline.

### Outcomes and data collection: objective 2: cost-effectiveness of the environmental cleaning bundle

Objective 2 outcomes and data measures and processes are shown in Table 3.

**Table 3 Tab3:** Objective 2 outcomes and data sources

Outcomes	Measures		Methods
Primary outcome: Incremental cost-effectiveness ratio from adoption of the cleaning bundle presented as cost per quality-adjusted life year (QALY) gained (calculated from secondary outcomes)			
Secondary outcomes:			
1. Changes in costs associated with implementing the bundle		Frequency and value of resources used in implementing the bundle (costs incurred)	Hospital specific items collated from existing hospital-based data sets and supplied to project team by trial site team for analysis. Centralised resources recorded by project team. Valued in 2016 Australian dollars (AUD)
		Cost of infection in terms of treatment costs, diagnosis costs and bed days saved (potential cost savings)	Calculated using estimates from the literature about the attributable cost of infection. Valued in 2016 AUD
2. Changes in QALYs associated with implementing the bundle		Opportunity cost of infection in terms of: 1. Deaths 2. QALYs	Calculated using estimates from the published literature on attributable mortality and morbidity for infection

The perspective used to evaluate the cost-effectiveness of the environmental cleaning bundle will be that of the health system. The timeframe will be the duration of the trial (62 weeks). All costs will be presented in Australian dollars for the current cost year 2016. Changes to health benefits will be estimated in quality-adjusted life years (QALYs). All costs and health benefits arising in future periods will be appropriately discounted [38].

#### Cost of implementing the bundle

Standard procedures for costing the intervention will be followed and all resources used to implement the intervention will be identified, measured and valued at local market prices [38]. The main resources used in implementing the bundle include staff time, costs of cleaning products, invisible gels, ultraviolet lamps and pathology costs. Resource use will be collected from each hospital by a monthly survey. Using a standardised tool across all hospitals and applying common cost vectors will ensure consistency in collection of costs across all sites and reduce uncertainty in estimates that often results from using retrospective administrative data. Staff time will be valued using full employment costs incurred at participating sites. Consumables will be valued at local market prices based on purchase contracts for each hospital.

#### Potential cost savings from implementing the bundle

If the bundle reduces infection rates, it should also produce cost savings. A reduced rate of infection should result in a lower average length of stay for patients and lower costs associated with diagnosis and treatment of infections [39]. Estimates of the number of antibiotics, screening and diagnostic tests and medical and surgical procedures avoided per infection will be based on standard treatment regimens for infection in participating hospitals and valued using hospital supplied unit costs. Estimates of the extra length of stay per infection avoided and the value of these bed days will be based on published estimates from recent high quality Australian studies [40, 41].

#### Change in health benefits from implementing the bundle

Changes to health benefits will be informed by estimating the deaths prevented, life years gained and QALYs gained as a result of fewer infections. The number of deaths averted will be estimated using Australian data on the attributable mortality associated with infection [42, 43]. We will also estimate years of life gained (accounting for observed age and comorbidities in the patient population), and finally, preference-based utility scores from the published literature [44] will be used to weight life expectancy, allowing the QALYs gained to be calculated.

#### Cost-effectiveness analysis

The incremental cost-effectiveness ratio (ICER) will be estimated by dividing the incremental change in total costs incurred and benefits gained due to implementing the bundle to give the incremental cost per QALY. Results will also be presented as the cost per infection prevented to allow comparison with other infection control interventions. The cleaning bundle will be considered cost-effective if the cost per QALY is less than $64,000, which is the willingness to pay for Australian QALYs and cost-saving if there is a net reduction in costs [45].

Probabilistic sensitivity analyses will be used to estimate the probability a decision to adopt the intervention is cost effective, given the current uncertainties in the observed parameters [46]. Sub-analyses will look at the efficiency of the cleaning bundle at individual hospitals to identify any systematic differences in the ICER that may be related to hospital characteristics.

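### The $64,000-per-QALY criterion is valid only when QALYs are gained; the probabilistic and hospital-level analyses need net monetary benefit at the same threshold

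*Protocol article*

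**What the plan says.** All of this is in the Protocol article, under objective 2.

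- **Outcome.** Table 3 gives the primary outcome as an ICER, "presented as cost per quality-adjusted life year (QALY) gained". The same table lists the change in QALYs as a secondary outcome that feeds the ratio.
- **Construction.** The section on cost-effectiveness analysis obtains the ratio by "dividing the incremental change in total costs incurred and benefits gained due to implementing the bundle to give the incremental cost per QALY".
- **Decision rule.** "The cleaning bundle will be considered cost-effective if the cost per QALY is less than $64,000". The same sentence adds a second label: "cost-saving if there is a net reduction in costs". It puts no condition on the sign of the QALY change, does not mention dominance and names no net-benefit criterion.
- **Uncertainty.** "Probabilistic sensitivity analyses will be used to estimate the probability a decision to adopt the intervention is cost effective". The article does not say by which quantity a draw is counted as cost-effective.
- **Hospitals.** "Sub-analyses will look at the efficiency of the cleaning bundle at individual hospitals to identify any systematic differences in the ICER".
- **Source of the health effect.** The section on change in health benefits describes "estimating the deaths prevented, life years gained and QALYs gained as a result of fewer infections". The section on potential cost savings derives savings from the same reduction in infections, and the section on the cost of implementing the bundle lists the resources that the bundle consumes.

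**The concern.** A ratio compared with a threshold gives the right decision only when its denominator is positive. When QALYs are lost, dividing by a negative number reverses the inequality, so a low ratio no longer means good value.

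This trial's model can reach that region easily. QALYs and savings both come from infections avoided. If an effect estimate or a draw points to more infections, QALYs fall and infection costs rise on top of the bundle's own cost. The result costs more and does less good, yet its ratio is negative and lies below $64,000.

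Two planned outputs are at stake. One is the probability that adoption is cost-effective, for which draws with QALY losses must be put on one side or the other. The other is the search for systematic differences between hospitals on a scale where a very good and a very bad result can share one value.

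**Working it through.** There is no stated figure to reproduce. The $64,000 is a threshold taken from a cited source, and the article gives no incremental cost or QALY values. All such values below are illustrative assumptions.

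**Step 1. Sign logic.** Let ΔC be incremental cost and ΔE incremental QALYs. The literal rule is ΔC/ΔE < 64,000. Net monetary benefit is NMB = 64,000 × ΔE − ΔC, and the bundle is worth adopting if NMB > 0.

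- If ΔE > 0, multiplying through gives ΔC < 64,000 × ΔE, which is NMB > 0. The two rules agree.
- If ΔE < 0, multiplying through reverses the sign: ΔC > 64,000 × ΔE, which is NMB < 0. The literal rule then passes exactly the results that should fail.

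**Step 2. The quadrants in numbers.**

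| Case | ΔC ($) | ΔE | Ratio ($) | Literal rule | NMB ($) | Rule correct? |
|---|---|---|---|---|---|---|
| Dearer, gain | +320,000 | +10 | 32,000 | pass | +320,000 | yes |
| Dearer, gain | +1,000,000 | +10 | 100,000 | fail | −360,000 | yes |
| Dominant | −100,000 | +10 | −10,000 | pass | +740,000 | yes |
| Dominated | +100,000 | −10 | −10,000 | pass | −740,000 | no |
| Cheaper, loss | −100,000 | −10 | 10,000 | pass | −540,000 | no |
| Cheaper, loss | −1,000,000 | −10 | 100,000 | fail | +360,000 | no |

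The dominant and dominated rows share one ratio, so no cut-off on the ratio can separate them. Barring negative ratios would wrongly reject the dominant row and would leave the last two rows wrong.

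**Step 3. Which quadrant matters here.** Write ΔC = B − s × ΔE, where B is the bundle cost and s the infection cost saved per QALY gained. With B > 0 and s ≥ 0, any ΔE < 0 gives ΔC > 0. Every QALY loss is then a dominated result. The two cheaper-with-loss rows need a bundle that costs less than current cleaning, so they are of little practical weight.

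**Step 4. Probabilistic analysis.** One million draws were made with assumed inputs: ΔE normal with SD 5 QALYs; B normal with mean $200,000 and SD $50,000; s = $5,000.

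| Mean ΔE | Passes literal rule | NMB > 0 | Dominated draws |
|---|---|---|---|
| +10 | 0.943 | 0.921 | 0.023 |
| +5 | 0.820 | 0.662 | 0.158 |
| 0 | 0.784 | 0.284 | 0.500 |
| −5 | 0.901 | 0.059 | 0.842 |

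The gap between the first two columns is the share of dominated draws, up to rounding (for example 0.284 + 0.500 = 0.784). Adding the condition ΔE > 0 to the ratio rule gives the NMB column. Under the literal rule, a bundle that on average does harm (0.901) looks better than one with no effect (0.784).

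**Step 5. Comparison between hospitals.** Keep B = $200,000 and s = $5,000, and take two hospitals close to zero effect.

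- ΔE = +0.5: ΔC = 200,000 − 2,500 = 197,500. Ratio 395,000. NMB = 32,000 − 197,500 = −165,500.
- ΔE = −0.5: ΔC = 200,000 + 2,500 = 202,500. Ratio −405,000. NMB = −32,000 − 202,500 = −234,500.

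The hospitals differ by one QALY and $5,000. Net benefit shows them as similar and both unfavourable. The ratio moves by 800,000 and changes sign.

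**The case against.** The strongest reply is that the ratio is defined for a QALY gain. Table 3 speaks of cost per QALY gained, the construction of the ICER divides by benefits gained, and the section on health benefits expects gains from fewer infections. On that reading a bundle that loses QALYs has no cost per QALY gained to set against $64,000. This stands for the headline result. A reader might infer that the plan would declare a dominated bundle cost-effective; the article nowhere says so, and its wording points the other way. It does not settle the matter for the other two analyses. If the rule is silent on QALY losses, the article has no stated criterion for draws that the promised probability must classify.

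Three further stronger readings should also be set aside.

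- *Accepting a negative ratio is itself an error.* It is not. Lower cost with more QALYs gives a negative ratio and is rightly cost-effective. The fault is confined to QALY losses.
- *The reported probability will be overstated.* The article names no metric for the probabilistic analysis, and a fuller analysis plan may well use net benefit. The gaps in the simulation arise only if draws are counted by the raw ratio.
- *One or two hospitals will be wrongly labelled cost-effective.* With a separate before-after estimate per hospital, 5 falling to 4 infections per 10,000 patient days, and an assumed 300 to 800 occupied beds, about 2.3 to 1.05 of 11 hospitals would be expected to show an effect of the wrong sign. The bed numbers are not in the article. The planned infection model has one intervention term and a random intercept, not hospital-specific effects. The section on cost-effectiveness analysis does not say that each hospital is classified against the threshold. The figure is conditional on all of this and is not a prediction.

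It is also fair to say that an ICER against a threshold is the declared outcome, and that adding a required QALY gain would be enough for the decision rule. It would not give the hospital comparison a scale that can be ordered.

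**Conclusion.** The point holds as a gap in a stated criterion, not as a plan to accept a harmful bundle. The $64,000 rule is correct for QALY gains and gives the reverse of the right answer for QALY losses. The wording elsewhere makes a wrong headline conclusion unlikely. The remaining exposure is in the probability of cost-effectiveness and in the comparison of ICERs across hospitals.

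The size cannot be fixed from the article. With the assumed inputs above, the literal rule and net benefit differ little when the bundle clearly works (0.94 versus 0.92) and greatly when it has no effect (0.78 versus 0.28). The sign logic in step 1 rests on no assumed values. This is an improvement at essentially no cost rather than a defect that threatens the trial.

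**What to change.** Replace the ratio rule in the section on cost-effectiveness analysis with wording such as: the bundle will be considered cost-effective if 64,000 × incremental QALYs minus incremental cost (net monetary benefit, in 2016 AUD) is greater than 0.

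Then add that:

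- the probability of cost-effectiveness is the share of probabilistic draws with positive net monetary benefit;
- hospitals are compared on net monetary benefit;
- the ICER remains the reported primary outcome of objective 2, with the result given as dominant (lower cost, more QALYs) or dominated (higher cost, fewer QALYs) where the ratio cannot be interpreted.

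The threshold, inputs, data and software do not change. The cost is a few lines of text.

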### Ethics approval

This project has received ethics approval from the Uniting Care Health Human Research Ethics Committee (approval number 1413) and the Queensland University of Technology Human Research Ethics Committee (approval number 1400000828). Local ethics approvals are being completed for all participating hospital sites.

### Trial status

At the time of manuscript submission, the REACH study is beginning year 2. The study team is completing the recruitment of trial sites, multi-site ethical applications and agreements prior to randomisation and allocation.

## Discussion

### Limitations

This trial requires 11 participating hospitals. It could be difficult to recruit that number as it is very likely that some hospitals will decline or be unable to participate. This could be due to a number of reasons, e.g. disinterest in research, a lack of resources, a concern about negative impact on hospital budgets due to the need to implement change and increased product use associated with participation. This will be addressed by following an established recruitment process that provides clear information about what is required and a focus on fostering engagement and relationships with key decision makers at each site.

Once enrolled, willingness to participate may waiver for sites that are randomised to later trial commencement times. This will be addressed by maintaining communication with all sites and through ongoing monitoring of site context and engagement. The potential for fatigue related to participation, especially for the longer intervention phase sites, will be managed through frequent monitoring and engagement activities at the trial site.

We recognise some possible limitations in relation to the ‘opt-in’ nature of the recruitment process (i.e. that participating hospitals may be those most receptive to change and quality improvement). To mitigate this, we will as much as possible approach a range of eligible hospitals and will ensure we complete comprehensive context mapping at each site to fully understand the barriers and enablers that may have influenced the site’s decision to participate.

Other limitations could occur due to adverse events occurring at the staff, patient or hospital level during the trial. This could include outbreaks of HAIs, seasonal factors, organisational or policy changes. This will be mitigated by frequent monitoring of each site. Participating sites will agree to not implement changes that could impact the trial, e.g. cleaning policies or product use, without prior agreement from the study team. If there is a serious national epidemic during the trial the study will continue to collect data, but any planned changeovers to the intervention will be delayed until the epidemic has passed.

### Significance

Previous cleaning research has often focused on single interventions, such as a new cleaning product or auditing strategy. However, implementing cleaning in a hospital setting is a multifaceted and complex process, where contextual factors influence the success of a new approach. This study, with its implementation science approach and emphasis on facilitation and local hospital context, will enable us to develop new insights into the processes and impacts of hospital cleaning. These will be used to assist with the translation of new knowledge from each of the trial sites to other hospitals in Australia and internationally.

The effectiveness and cost-effectiveness of a cleaning bundle intervention will be evaluated to support evidence-based decision-making in public and private healthcare sectors about the impact of investment in an environmental cleaning programme in acute hospitals, particularly on the risks of HAIs. It will further show whether this policy is cost-effective in a real world setting, addressing an identified research gap [7].

## Abbreviations

ACSQHC: Australian Commission on Safety and Quality in Health Care
ANZCTR: Australia New Zealand Clinical Trial Registry
ATP: adenosine tri-phosphate
AUD: Australian dollar
CDI: *Clostridium difficile* infection
CRE-RHAI: Centre of Research Excellence in Reducing Healthcare-Associated Infections
GLMM: generalised linear mixed model
HAI: healthcare-associated infection
ICER: incremental cost-effectiveness ratio
ICU: intensive care unit
iPARIHS: integrated Promoting Action on Research Implementation in Health Services
MRSA: methicillin-resistant *Staphylococcus aureus*
NHMRC: National Health and Medical Research Council
NHPA: National Health Performance Authority
QALY: quality-adjusted life years
REACH: Researching Effective Approaches to Cleaning in Hospitals
RLU: relative light unit
SAB: *Staphylococcus aureus* bacteraemia
UV: ultraviolet
VRE: vancomycin resistant enterococci
